### Follow-up visits and monitoring schedule

2.8

The study will start with a 7-day preliminary phase where eligible individuals will provide their consent and initial information will be gathered. Future appointments will be planned for 6 days ± 1 day (visit 1), 4 weeks ± 3 days (visit 2), and 12 weeks ± 3 days (visit 3) after starting the treatment. Follow-up assessments will be conducted at Week 12 ± 7 days post-discontinuation of treatment (24W ± 7d) (visit 4). To minimize loss to follow-up, participants will be regularly contacted through telephone calls and WeChat group communication. Reminders will be provided before each scheduled visit to improve retention and adherence. Table 1 outlines the comprehensive assessment timetable.

**Table 1 T1:** Schedule of enrollment, interventions, and assessments.

Study phase time	Lead-in period	Treatment period			Follow-up period
	Screening (−7D-0D)	Baseline (6D ± 1d)	Week 4 (4W ± 3d)	Week 12 (12W ± 3d)	Week 24 (24W ± 7D)^a^
Patients					
Eligibility screen	X				
Inclusion/exclusion criteria	X				
Informed consent	X				
General information	X				
Medical history	X				
Allocation	X				
Pregnancy examination	X				
Outcomes					
Primary outcome					
6-minute walk test	X	X	X	X	X^c^
Secondary outcomes					
BNP	X	X	X	X	X
MACE (including cardiac death, non-fatal myocardial infarction, and rehospitalization due to heart failure) ^b^	X	X	X	X	X
NYHA classification	X	X	X	X	X
KCCQ quality of life score	X	X	X	X	X
Exploratory outcomes					
Diuretic usage		X	X	X	X
Echocardiography	X			X	X
Heart failure-related rehospitalization rate^b^	X	X	X	X	X
TCM syndrome score	X	X	X	X	X
Myocardial enzyme levels	X			X	X
Inflammatory markers and other biochemical indicators	X			X	X
Safety					
Vital signs	X	X	X	X	X
Biochemical indexes	X			X	X
Electrocardiogram results	X			X	X
Adverse events	X	X	X	X	X
Others					
Drug distribution	X		X		
Drug recycle			X	X	
Combined medication			X	X	
Confirmation of medication compliance		X	X	X	X

a Visit 4 corresponds to the follow-up assessment conducted at Week 24, which is 12 weeks after completion of the 12-week treatment period, as stated in manuscript.

b Continuous monitoring throughout the study.

c Primary endpoint assessed at week 24.

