### Sample size calculation

2.14

Patients will be randomized in a 1:1 ratio to receive either FJHQG or placebo. Previous studies in HF suggested that improvements of approximately 30 meters in the 6MWT is clinically meaningful. According to our previous clinical observation, assuming FJHQG demonstrates an improvement of 50 meters in 6MWT compared with placebo and a standard deviation of 72 meters among two groups, a two-sided significance level of *α* = 0.05, and a statistical power of 90%. The results indicate that at least 45 patients will be needed per group. Considering an anticipated dropout rate of 10%, a total of 100 patients will be enrolled, with 50 allocated to the intervention group and 50 to the placebo group. The study is powered for the primary functional endpoint and is not designed to detect differences in clinical events.

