The primary outcome (6-minute walk test) will be analyzed using analysis of covariance (ANCOVA) with baseline values and key covariates (age, sex) as covariates to adjust for potential confounding. Secondary outcomes, due to their diverse nature, will be analyzed using appropriate methods: continuous variables with t-test or Wilcoxon test, categorical variables with Chi-square or Fisher's exact test, and repeated measures or longitudinal data using linear mixed-effects models. To control for multiple comparisons among secondary outcomes, the false discovery rate (FDR) adjustment using the Benjamini-Hochberg method will be applied, and a hierarchical structure will be applied with the primary outcome taking precedence over secondary and exploratory outcomes. The primary analysis will be conducted according to the intention-to-treat (ITT) principle, including all randomized participants. If the proportion of missing 6MWT data is 5% or greater, missing data for the 6MWT will be handled using multiple imputation under the missing-at-random assumption. The imputation model will include baseline 6MWT value, age, sex, and treatment group as predictors. Imputation will be performed using a single model based on all available data without separating treatment arm. In addition, reasons for missing data will also be recorded, categorized, and summarized descriptively, and will be compared between groups. Prespecified subgroup analyses will be conducted based on heart failure phenotype, defined by left ventricular ejection fraction (LVEF ≥50% vs. <50%), and by sex. These subgroup analyses will be considered exploratory. Sensitivity analyses will be performed, including per-protocol analyses and complete-case analyses, to assess the robustness of the results. Deaths occurring before the final assessment will be handled in sensitivity analyses using a worst-case approach by assigning a value of zero for the 6MWT, representing the worst functional outcome. Adverse events will be summarized in tables and compared between groups using descriptive statistics. All analyses will be performed using SAS software version 9.4, and two-tailed *P*-values < 0.05 will be considered statistically significant. A detailed statistical analysis plan will be finalized prior to database lock to ensure prespecified analysis procedures.

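### The 5% trigger for imputing the 6MWT conflicts with a primary analysis of all randomised participants, and neither branch uses the Week 4 and Week 12 walks

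*Protocol article*

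**What the plan says.** All of this is in the protocol article.

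- **Statistical analysis (2.15), population:** "The primary analysis will be conducted according to the intention-to-treat (ITT) principle, including all randomized participants".
- **Same section, next sentence:** "If the proportion of missing 6MWT data is 5% or greater, missing data for the 6MWT will be handled using multiple imputation", under a missing-at-random assumption. No method is named for a smaller amount of missing data.
- **Same section, models:** the primary model is an ANCOVA on the 6MWT with baseline, age and sex as covariates. The imputation model lists baseline 6MWT, age, sex and treatment group. Complete-case analysis appears only as a sensitivity analysis. Linear mixed-effects models are named for longitudinal data among the secondary outcomes.
- **Follow-up visits and monitoring schedule (2.8), Table 1:** the walk is scheduled at screening, at the day-6 visit and at Weeks 4, 12 and 24. A footnote reads "Primary endpoint assessed at week 24".
- **Sample size calculation (2.14):** 45 evaluable per group, 10% dropout allowed for, 100 randomised.

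**The concern.** Two statements about the same analysis do not fit together. One puts all randomised participants in the primary analysis. The other gives a way of keeping those without a Week 24 walk only once enough of them are missing. An ANCOVA cannot use a participant who has no outcome value, so below the trigger the promise is not kept, and the sensitivity analysis meant to test it tests nothing.

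The second problem lies above the trigger. Imputation helps the estimate only if it brings in information that the analysis model lacks. The listed predictors bring none, although walks at Weeks 4 and 12 will exist for most people lost late. The missing-at-random assumption is then conditional on baseline, age, sex and arm alone. That is weaker protection than the collected data allow: someone doing badly at Week 12 may be less likely to return at Week 24.

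**Working it through.** **The plan's own figure.** Inputs from 2.14: difference 50 m, SD 72 m, two-sided alpha 0.05, power 90%.

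- Normal approximation: n = 2 × (72 × (1.960 + 1.282) / 50)² = 43.6, rounded up to 44.
- The t-test version gives 44.6, rounded up to 45, as stated.
- Dropout: 45 / 0.90 = 50 per group, 100 in total.

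The sample size reproduces and is not affected by this point.

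**Who is analysed below the trigger.** The denominator is Week 24 values among 100 randomised.

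| Week 24 walks missing | Share | Imputation | In primary ANCOVA |
|---|---|---|---|
| 1 to 4 | 1% to 4% | none | 99 to 96 |
| 5 | 5% | yes | 100 |
| 10 (planned dropout) | 10% | yes | 100 |

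The exclusion in the first row is inferred: no method is named there, and ANCOVA alone drops such cases. The trigger pools the arms, so 4 missing against 0 (4/50 = 8% of one arm) does not set it off, while 3 against 2 does. Power is hardly touched: 46 against 50 gives 92.5%.

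**What imputation adds above the trigger.** The ANCOVA terms are treatment, baseline 6MWT, age and sex. The imputation predictors are the same four. When only the outcome is missing, values drawn from the analysis model's own regression carry no new information, so the pooled estimate equals the complete-case estimate apart from Monte Carlo noise.

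**Size of the bias if loss depends on the Week 12 walk.** Assumptions:

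- true effect 50 m and SD of change 72 m (both from 2.14);
- correlation r between Week 12 and Week 24 changes of 0.7 (not in the documents);
- 4 of 50 drug-arm participants lost, none in the placebo arm.

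If the lost participants lie d SDs below their arm's mean at Week 12, the mean of the 46 observed rises by (4/46) × d × r × 72.

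- Four at random from the worse half, d = √(2/π) = 0.80: (4/46) × 0.798 × 0.7 × 72 = 3.5 m, or 3.5/50 = 7% of the planned effect.
- The four worst of 50, d about 1.80 (normal order statistics): (4/46) × 1.80 × 0.7 × 72 = 7.9 m, or 16%.
- Range over r: at r = 0.5, 2.5 m and 5.6 m; at r = 0.9, 4.5 m and 10.1 m.

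The sign reverses if the losses are in the placebo arm. Equal losses of the same kind in both arms cancel.

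**Simulation** (baseline SD assumed 90 m; age and sex not simulated):

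| Four worst drug-arm Week 12 changers lost | Estimated effect |
|---|---|
| Full data | 49.8 m |
| Complete-case ANCOVA | 57.8 m |
| Multiple imputation, baseline and arm | 57.8 m |
| Multiple imputation, Week 12 walk added | 49.9 m |

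In a separate run, four losses at random from the worse half gave 53.4 m by complete-case against 50.1 m with full data. Four losses at random from the whole drug arm gave 50.1 m, that is, no bias.

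**The case against.** **The conflict touches few people and is unlikely to arise.** It affects at most 4 of 100. At a true 10% dropout with independent losses, the chance of 4 or fewer missing is only 2.4%. This stands, and it makes the all-randomised conflict mainly one of wording. It does not answer the predictor problem, which applies above the trigger, where the trial expects to be.

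**The scenarios are adverse.** Four random losses fall in one arm only about 12% of the time, and losing exactly the four worst is an extreme case. Random loss gives no bias. This also stands, so the 8 m is an outer case and the 3.5 m is the more useful figure.

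**The detail belongs in the SAP.** The article says that one will be finalised before database lock. But the threshold and the predictor list are stated in the article, so this is a rule fixed badly and not a detail left open.

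**Two stronger readings should be resisted.**

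- A reader might blame the bias on the 5% threshold. The simulation contradicts this: with the listed predictors, turning imputation on changes nothing.
- A reader might also count all scheduled walks and conclude that imputation would be off at the planned dropout, since 10 people missing only Week 24 are 10/500 = 2%. No denominator is written, so this is not strictly excluded. But the rule directly follows the sentence on the primary analysis, and both Outcomes (2.9) and the Table 1 footnote place the primary outcome at Week 24. On that natural reading the share is 10/100 = 10%, and imputation is on.

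**Conclusion.** The point holds in two parts. First, below 5% the stated rule cannot deliver the promised analysis of all randomised participants, and the complete-case sensitivity analysis duplicates the primary one. Second, above 5% the imputation as specified retains those participants in name but gives essentially the complete-case estimate, because it leaves out the Week 4 and Week 12 walks.

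For a given set of losses the two branches carry the same bias. With 4 one-sided drug-arm losses related to the Week 12 walk it is about 3.5 m in the moderate case and about 8 m at the extreme. These sizes rest on the assumed 0.7 correlation and on loss that is unequal between arms. The bias is nil if loss is random. The sample size and power are sound. This is a cheap improvement to the primary analysis, not a flaw that undermines the trial.

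**What to change.** Delete the 5% condition and state that missingness refers to the Week 24 value. Whatever the amount missing, use one of the following as the primary analysis:

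- a linear mixed model fitted to the scheduled post-baseline walks, adjusted for baseline 6MWT, age and sex, reporting the treatment difference at Week 24; or
- multiple imputation in every case, with the Week 4 and Week 12 walks added to the imputation model, followed by the planned ANCOVA.

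Always imputing with the present predictors would settle the wording but leave the bias. Keep complete-case as the sensitivity analysis, where it then becomes a real comparison. The cost is a sentence or two in the protocol or SAP and slightly more programming. No extra participants, visits or measurements are needed.

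### As specified, multiple imputation of the week 24 walk reproduces the complete-case result, because the week 4 and week 12 walks are not among its predictors

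*Protocol article*

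**What the plan says.** Section 2.15 of the protocol article defines the primary analysis as an ANCOVA of the 6MWT with the baseline walk, age and sex as covariates. Once missing 6MWT data reach 5%, they are multiply imputed under missing at random. The predictors are listed: "The imputation model will include baseline 6MWT value, age, sex, and treatment group as predictors". The next sentence specifies one imputation model for both arms together. On robustness the section says: "Sensitivity analyses will be performed, including per-protocol analyses and complete-case analyses, to assess the robustness of the results". It adds a sensitivity analysis that sets the walk to zero after death, and a between-group comparison of the reasons for missing data.

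In Table 1 (section 2.8) the row "6-minute walk test" is marked at screening, at a day 6 visit labelled as baseline, and at weeks 4, 12 and 24. The primary endpoint is week 24, twelve weeks after treatment stops. Section 2.14 plans for dropout: "Considering an anticipated dropout rate of 10%, a total of 100 patients will be enrolled".

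**The concern.** Imputation improves on complete-case analysis when the imputation model holds information that the analysis model lacks. Here the two sets of named terms are the same. The walks most likely to predict both the missing week 24 value and the decision to leave are those at weeks 4 and 12, and they are not listed. Missing at random is thus assumed without the data that would make it most plausible.

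Two things are at stake. If dropout depends on how a participant was walking at week 12, and differs by arm, the primary estimate carries a bias that the scheduled data could have reduced. And the complete-case analysis will agree with the primary analysis whatever the dropout mechanism, so their agreement is no evidence that missing at random holds. The rule is likely to come into play, because the anticipated dropout of 10% is twice the 5% trigger.

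**Working it through.** **1. The plan's own sample size.** Inputs from section 2.14: "assuming FJHQG demonstrates an improvement of 50 meters in 6MWT compared with placebo and a standard deviation of 72 meters among two groups", two-sided alpha 0.05, power 90%, 1:1 allocation.

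n per arm = 2 × (1.960 + 1.282)² × 72² / 50² = 43.6, so 44 by the normal approximation. With the noncentral t distribution, power is 89.6% at 44 and 90.3% at 45, so 45 per arm, and 45 / 0.9 = 50. This matches "at least 45 patients will be needed per group" and the total of 100. The sample size is not in question.

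**2. Why the two estimates coincide.** Let X hold intercept, arm, baseline walk, age and sex, split into rows with the week 24 walk observed (Xo, yo) and missing (Xm).

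- Complete-case estimate: b = (Xo′Xo)⁻¹ Xo′yo.
- Imputed values have mean Xm b, averaged over imputations.
- ANCOVA on completed data, averaged over imputations: (X′X)⁻¹ (Xo′yo + Xm′Xm b) = (X′X)⁻¹ (Xo′Xo + Xm′Xm) b = b.

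So the imputed estimate converges to b as the number of imputations grows. The same holds for change from baseline, because baseline is a covariate. This result needs no assumption about dropout or correlations. It needs complete covariates and matching terms.

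**3. Simulation.** Inputs from the protocol: 50 per arm, effect 50 m, SD 72 m. Assumptions not in the documents: correlations with week 24 of 0.5 (baseline), 0.7 (week 4) and 0.8 (week 12); the missingness rates; the dropout mechanisms. There were 1,000 trials per scenario and 50 imputations. Entries are the mean estimate in metres, with mean SE in brackets; the true value is 50.

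| Missing, mechanism | Complete case | Imputation as written | Weeks 4 and 12 added |
|---|---|---|---|
| 10%, completely at random | 50.06 (13.32) | 50.05 (13.37) | 50.03 (12.98) |
| 10%, depends on baseline | 49.70 (13.29) | 49.69 (13.35) | 49.76 (12.96) |
| 5%, poor week 12 walk, active arm only | 52.64 (12.88) | 52.63 (12.91) | 49.86 (12.81) |
| 10%, same | 55.24 (13.17) | 55.22 (13.22) | 50.12 (12.99) |
| 20%, same | 57.81 (13.91) | 57.83 (14.01) | 49.29 (13.48) |

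At 10% missing, the first two columns correlate 0.999 across trials. The SD of their difference is 0.6 m with 50 imputations and 0.1 m with 2,000, which is Monte Carlo noise.

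Precision gain at 10%, completely at random: (13.37 − 12.98) / 13.37 = 2.9%.

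**4. Range over the assumptions.** Complete-case analysis stands in for the planned imputation here, as step 2 allows.

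- Dropout in one arm only, with a week 12 to week 24 correlation of 0.6 to 0.7: bias about +1.7 m at 10% missing and +3.4 m at 20%. These figures also depend on how steeply dropout is assumed to rise as the week 12 walk worsens.
- Dropout in both arms on a poor week 12 walk relative to the arm's own mean: mean estimate 49.7 to 50.3 m at 10% and 20%, so no material bias.

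The one-arm range is therefore about +2 to +5 m at 10% missing and +3 to +8 m at 20%.

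**The case against.** **The material bias needs a particular mechanism.** It arises when dropout depends on the week 12 walk and does so differently by arm. Nothing in the documents points to this in a double-blind trial with a matched placebo, and the neutral scenarios show little or no bias. This stands. A reader might infer that the primary result will be off by 5 to 8 m; the documents do not support that. Even in the adverse case at 10% missing, 5.2 m is about 0.4 of a standard error (5.2 / 13.2).

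**Other checks exist.** A reader might infer that the sensitivity analyses as a whole are empty. They are not: the per-protocol analysis, the zero value after death and the comparison of reasons for missing data all differ from the primary analysis. But the per-protocol and death analyses do not probe missing at random for participants who drop out alive, and comparing reasons may reveal uneven dropout without correcting for it. Nor does the protocol claim that the complete-case analysis is independent of the primary one.

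**Three walks are not discarded.** It is tempting to count the day 6 walk as well. Table 1 labels that visit as baseline, so it may already be in the model. The point rests on weeks 4 and 12.

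**The matching of terms may not be exact.** Sections 2.7 and 2.15 promise adjustment for background treatment. If that enters the primary ANCOVA, the two estimates no longer coincide exactly, but the stated imputation model then omits an analysis covariate, which also needs correcting. The primary-analysis sentence names only the baseline walk, age and sex.

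**The SAP may add to the list.** The protocol says that a detailed SAP will follow, and the list of predictors is not expressly closed. Yet the predictors are stated, and a SAP that follows them inherits the problem. The reference to all available data does not extend the list: it occurs in the sentence about modelling the arms together and describes which records are pooled.

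**The remedy has a limit.** It helps only for participants who reach the interim visits, and the documents give no dropout timing. This stands.

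**Conclusion.** The point holds as a weakness of the stated imputation model. With complete covariates, only the week 24 walk missing and the ANCOVA as named, the planned imputation gives the complete-case answer; this is algebra and does not depend on the simulation assumptions. The complete-case analysis therefore cannot serve as a check on missing at random.

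How much this matters is conditional. The biases in the working rest on assumed correlations and on dropout driven by the week 12 walk in one arm only. The precision forgone is small. The finding does not show that the primary analysis is wrong or that its result will be biased. It is a worthwhile correction to make before database lock, not a fatal defect.

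**What to change.** In section 2.15, and in the SAP when it is finalised:

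- Add the week 4 and week 12 6MWT values to the imputation model. Keep baseline 6MWT, age, sex and treatment group, and include any background-treatment covariate that enters the primary ANCOVA.
- State how interim walks that are themselves missing will be imputed, for example sequentially by visit.
- Keep the complete-case analysis if wanted, but do not present it as the check on missing at random.

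Optional: a delta-adjusted analysis would probe missing at random for living dropouts, and a mixed model for repeated measures is another way to use the interim walks. Neither is required to resolve the point.

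The cost is a few sentences and modest programming. No extra visits or data are needed, because Table 1 already schedules these walks.

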## Discussion

3

According to guideline recommendations, the primary treatment for HF includes ACEIs/ARNIs, sodium-dependent glucose transporters 2 inhibitors, beta-blockers, and mineralocorticoid receptor antagonist, etc (16). However, research indicates that the mortality rate for HF patients within one month of discharge, even after receiving conventional drug therapy remains high (17). This trial a randomized, double-blind, placebo-controlled, parallel-group trial that aims to assess the safety and clinical efficacy of FJHQG as an adjunctive treatment for HF. This trial is designed to provide preliminary clinical evidence supporting the potential application of FJHQG in HF treatment.

It has been demonstrated that FJHQ decoction has various pharmacological effects in different diseases (8). Regarding cardiovascular disease, FJHQ decoction has shown its effects in improving cardiac function in patients with HF. It has been demonstrated that FJHQ decoction improved ejection fraction, increased 24-hour urine production, reduced NT-proBNP levels, and relieved symptoms of HF (9, 10). In addition, we previously conducted a clinical trial with 74 patients suffering from HF with preserved ejection fraction and found that FJHQ decoction significantly reduced symptoms like shortness of breath and fatigue. Additionally, FJHQ decoction also improved the results of the 6-minute walk test and reduced serum BNP levels, the mechanism of which was associated with the reduction in serum sST2 and galectin-3 levels by FJHQ decoction (18). Moreover, it has also been found that FJHQ decoction is effective in improving renal function and increasing renal blood flow, which is also correlated with amelioration of cardiac function (19). Network pharmacology analyses have suggested that the potential effects of FJHQ decoction may involve modulation of neurohumoral signaling, vascular function, and myocardial stress–related pathways relevant to heart failure pathophysiology (20). Collectively, these findings provide a clinical and mechanistic rationale for the present randomized controlled trial.

Several limitations should be noticed in this trial. Firstly, the limited timeframe of the study will result in a short follow-up period for this trial. Long-term efficacy of FJHQG requires extended follow-up. Secondly, the current study will exclude participants with HF aged over 80, raising concerns about whether the results will apply to those over 80 years of age. Thirdly, the assumed effect size may be relatively optimistic and should be interpreted in the context of an exploratory study design. Finally, our study population will consist predominantly of Han Chinese individuals from southern China. Therefore, it will remain unclear whether the results can be generalized to different ethnic and regional groups.

In conclusion, this research will assess the efficacy and safety of FJHQG in patients with HF and will explore the fundamental mechanisms, providing fresh perspectives on HF treatment.
